### 3.4 Secondary Study Endpoints:

1. Impact of the survivorship programme on quality of life.
  - EORTC QLQ C30 will be administered at baseline and at the end of the 12-week programme.
  - Quality-adjusted life-year (QALY) (EQ-5D-5L)
  - ASAS-R assessment
  - Additional Assessments as identified by the scoping review will be included in the Expansion Phase.
2. Impact of the survivorship programme on cancer related fatigue.
  - Cancer related fatigue score(EORTC QLQ-FA12).
3. Impact of the programme physiotherapy and dietetic interventions:
  - Maintenance of weight (weight measurement); changes in body composition (lean body mass and fat mass as measured by Bioelectrical Impedance Analysis [BIA]); muscle strength and mass (8 repetition maximum, thigh circumference); physical function and cardiovascular fitness (grip strength, 6 minute walk test [6MWT]).
  - An analysis of body composition analysis using US for muscle mass assessment compared to BIA in a subset of men participating in the study.
  - Changes in dietary intake and diet quality over the study period resulting from the dietetic intervention.
  - Dietary assessments will be conducted by a dietitian. This includes two 24 Hour Dietary Recalls and the WCRF food checklist at baseline and the programme endpoint (12 weeks) and a Food Frequency Questionnaire at baseline and 6 month follow up.
4. Self-care agency and its relationship to quality of life and symptoms experienced.
  - Instruments to measure self-care agency include the ASAS-R
  - Additional Assessments as identified by the scoping review will be included in the Expansion Phase.
5. The resource utilisation of signposted services among participants in the 12-week intervention programme.
  - Quality-adjusted life-year (QALY) (EQ-5D-5L)
  - Resource utilisation (number of signposted resources used). (See section 4.4.4)
6. Satisfaction of participants and Health Care Professionals with the programme and their perceptions of the systems usability.

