#### **Anthropometric measures:**

- **Body weight:** Weight will be recorded with the participant wearing light clothes and no shoes on the same scale at the baseline visit and at the programme endpoint (12 weeks). Patients will also self-assess their weight using the same personal scales at home, at the same time of the day, at baseline and at the endpoint of the study. Participants will report their weight on the same day their weight has been recorded at home through their regular ePRO surveys.
- **Height:** The participant's height will be measured at baseline.
- **Body Mass Index (BMI):** This will be calculated using the participant's weight and height and is part of the WCRF/AICR scoring system.
- **Body Composition:** Segmental body composition will be analysed using Bioelectrical Impedance Analysis (BIA) with the Body Composition Monitor (BCM) (Fresenius Medical Care, Bad Homburg, Germany) for all participants. This is used for an accurate and objective assessment of overall body composition and hydration status [9]. The BCM device calculates the lean tissue mass (LTM), lean tissue index (LTI), fat tissue index

(FTI), body cell mass (BCM), and adipose tissue mass (ATM), extracellular (ECW), intracellular (ICW) and total body water (TBW) based on measurement values, using physiological modelling and mixture equations (Cole-Cole plot and Hanai formulae and Chamney et al, 2007 [10]). Body composition using BIA will be assessed at baseline and the intervention completion (12 week) timepoints. Some patients may also have body composition analysis using a handheld ultrasound Vscan Air™ (GE HealthCare, 2023), for muscle mass assessment by an appropriately trained member of the study intervention team.

- **Waist circumference:** This measurement will be recorded with the participant not wearing clothing that is directly over the skin. If this is not possible, the measurement may be taken over light clothing. This is also part of the WCRF/AICR standardised scoring system.
- **Muscle strength:** Hand grip strength (HGS) will be measured using the Jamar dynamometer (Jamar Hydraulic Hand Dynamometer, Model 091011725, Sammons Preston Roylan, Nottinghamshire, UK) with its handle in the second position as recommended by the American Society of Hand Therapists (ASHT) [11]. Grip strength will be measured 3 times per hand, alternating between left and right hand to allow rest and account for any fatigue.

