- **Nutritional risk:** Participant's nutritional status will be monitored over the 12-week period on the study database by assessing any change in their Body Composition and MST score, see below.

**Dietary quality** will be measured using the WCRF/AICR standardised scoring system which was discussed earlier. This also includes assessment of their alcohol intake.

**Dietary intake:** Dietary assessments will be conducted by a dietitian. This includes two 24 Hour Dietary Recalls and a Food Frequency Questionnaire at baseline and month 6 (questionnaire follow up). Portion sizes will be validated through the use of a food atlas.

Additional detail on instruments for data collection of the Nutritional & Anthropometric assessments are provided here:

- **24 Hour Dietary Recall:** Following assessment of the 24h diet recalls, the programme dietitian will assign appropriate food codes to each item reported. Data analysis will be limited to the McCance and Widdowson's composition of foods integrated dataset, the USDA Food Composition Databases and the Irish food composition databases. Food coding will be completed following each individual dietetic assessment. A food code data base will be generated and expanded upon following extraction of new food codes from each new 24hour diet recall recorded. This data will be analysed using Nutritics, web-based nutritional analysis software to capture diet intake assessing macro- and micronutrients, and specific food and nutrients directly relating to the dietary quality outlined in the WCRF framework for cancer prevention. All reference data will be assessed within-individual comparison and between-individual comparison. All data will be exported from Nutritics into a Microsoft excel file for processing with the study statistician.

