- Food Frequency Questionnaire:** Individual and collective sample data captured from the EPIC-Norfolk Food Frequency Question (FFQ) will be entered in to the FFQ processing tool, FETA (Φετα) FFQ EPIC Tool for Analysis, which is based on the earlier CAFÉ system [12]. The FETA tool is free to use and will produce different levels of nutrient data, as well as basic food groups and food patterns. This programme is based on version 6 (CAMB/PQ/6/1205) of the EPIC-Norfolk Food Frequency Questionnaire (FFQ). FETA calculates the average daily intake of 46 nutrients and 14 food groups, for each individual. The default nutrients list provides a description of each nutrient/food group and the units used. The nutrient data for the FFQ foods have come from McCance and Widdowson's "The Composition of Foods (5th edition)" and its associated supplements. In FETA, the frequency category is converted into a portion multiplier (e.g. once a week =  $1/7 = 0.14$ ). After multiplication with the portion size, an average daily food weight for each of the 130 FFQ items is obtained. These weights are multiplied by the nutrient composition per gram to obtain the nutrient composition of the actual amount eaten. After summing all FFQ items for a participant, an average daily nutrient intake is obtained. Individuals with more than 10 missing lines of data will be excluded. The top and bottom 0.5% of the ratio of energy intake to estimated basal metabolic rate will be flagged as extreme outliers of nutrient intakes. All data will be exported from FETA data processing report into a readable Microsoft excel file for processing by the study statistician.
- Malnutrition Screening Tool:** The MST is a simple, quick, valid and reliable tool which can be used to identify patients at risk of malnutrition. It asks participants if they have lost weight recently without trying (and if so, how much) and if they have been eating poorly because of a decreased appetite [13]. Patients identified at nutritional risk, will be advised on an appropriate nutrition care plan. Some patients may require ongoing monitoring, nutritional counselling and review of personal nutrition care plans. These patients will be invited to attend the ongoing dietitian clinic. The need for follow up review and number of sessions required for each patient will be decided by the programme dietitian based on clinical judgment.

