- Physical activity:** a short validated physical activity questionnaire will be used [14] to measure physical activity levels. Physical activity is a fundamental Cancer Prevention Recommendation of the World Cancer Research Fund/American Institute for Cancer Research (WCRF/AICR) framework for cancer prevention. It will be measured as moderate to vigorous physical activity in minutes per week. The data for physical activity will be collected by the physiotherapist, which the dietitian will extract and place in a scoring system. It will be included in the (WCRF/AICR) standardised scoring system [8]. This is a practical tool that operationalises eight out of ten 2018 WCRF/AICR cancer prevention recommendations. The score enables researchers to assess the degree to which people adhere to the Cancer Prevention Recommendations and the health effects of doing so. The WCRF/AICR score is an accumulation of points assigned for adhering – or not adhering – to each of the components of the Cancer Prevention Recommendations or sub-recommendations. However, physical activity won't be included in the triggers.

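### Diet quality is measured by the total WCRF/AICR score, which also counts BMI, waist and physical activity, so it can rise with no change in diet

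*Protocol*

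**What the plan says.** Section 3.4 lists as a secondary endpoint "Changes in dietary intake and diet quality over the study period resulting from the dietetic intervention". Section 2.3 has a matching objective, which evaluates the dietetic intervention through dietary intake and diet quality.

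Section 4.4.4.1 fixes the instrument: dietary quality "will be measured using the WCRF/AICR standardised scoring system which was discussed earlier". It adds that alcohol intake is covered. Elsewhere the same section states what else goes into the score:

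- BMI: "This will be calculated using the participant's weight and height and is part of the WCRF/AICR scoring system".
- Waist circumference: "This is also part of the WCRF/AICR standardised scoring system".
- Physical activity: "It will be measured as moderate to vigorous physical activity in minutes per week", and "It will be included in the (WCRF/AICR) standardised scoring system".

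The physical activity entry describes the score as points added up over components that cover eight of the ten WCRF/AICR recommendations. It leaves physical activity out of the triggers, but not out of the score. No diet-only sub-score is named, and no points or cut-offs are given.

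The Schedule of Activities (section 5.0) places the WCRF/AICR questionnaire at screening and at end of treatment.

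**The concern.** The construct named and the construct measured differ. Diet quality is what the men eat and drink. The score that stands for it also gives credit for body size and exercise.

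This matters because the programme acts directly on one of the non-diet components. The men whose diet is being assessed are also in supervised exercise, and all of them receive both parts, so no comparison within the study separates the two. A rise in the total could come from the exercise classes, from a change in body weight, from diet, or from any mixture of these, and the endpoint wording would credit it to the dietitian's work.

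The design in section 3.1 asks what works, for whom and under what circumstances. A mixed total reported as diet quality is a poor answer to that for the dietetic part of the programme.

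**Working it through.** The protocol states no figure for this endpoint, so there is none to reproduce. The check sets the relevant text side by side and then bounds the size under stated assumptions.

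**1. What the score contains.** From section 4.4.4.1: food and drink items, alcohol, BMI, waist circumference, and moderate-to-vigorous minutes per week. The points are summed. BMI, waist and activity are not diet.

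**2. What the programme does to a non-diet component.** Section 4.4.3.1 gives two combined resistance and aerobic sessions a week of about 60 minutes each:

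2 × 60 = 120 supervised minutes per week.

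This is an upper bound on what the classes add to the activity item. The protocol does not say whether resistance work counts as moderate-to-vigorous activity. Home exercise of moderate intensity is encouraged on top.

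**3. When the score is taken.** End-of-treatment assessments fall in week 12 or within two weeks of completing the programme (section 5.0), so during the classes or shortly after them. No recall window for the activity questionnaire is stated.

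**4. Share of the score outside diet.** The protocol gives eight recommendations but neither lists nor weights them. Assume equal weight, with BMI and waist together forming one recommendation, physical activity another, and the rest dietary:

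- Physical activity: 1/8 = 12.5%.
- BMI and waist: 1/8 = 12.5%.
- Together: 2/8 = 25%.
- If only seven recommendations apply to these men (a further assumption): 2/7 = 28.6%.

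**5. Movement in the mean with diet unchanged.** Suppose each recommendation is worth at most 1 point (assumption), and a fraction f of men gain p points on physical activity alone. The mean total then rises by f × p:

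| f | p = 0.5 | p = 1 |
|---|---|---|
| 0.25 | 0.125 | 0.25 |
| 0.50 | 0.25 | 0.50 |
| 1.00 | 0.50 | 1.00 |

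The range is 0.125 to 1.0 point. These values of f and p are illustrations, not estimates. A man already at the top activity category at baseline gains nothing.

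**The case against.** The strongest reply is that diet-only evidence is already planned. Section 3.4 has two 24-hour recalls and the WCRF food checklist at baseline and 12 weeks, and a food frequency questionnaire at baseline and 6 months. Section 4.4.4.1 says the recalls will be analysed for foods and nutrients that bear on dietary quality in the WCRF framework. This stands. An unchanged diet would be visible there, so a reader who infers that the dietetic objective goes unanswered would be going too far. But section 4.4.4.1 uses the recalls and the frequency questionnaire for dietary intake, and nowhere is the checklist named as the diet-quality measure.

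Second, dietetic education in section 4.4.3.2 covers lifestyle as well as diet and follows the WCRF recommendations, and the bullet in section 3.4 sits under a joint physiotherapy and dietetic heading. A total adherence score is a reasonable outcome for such a programme. That supports keeping the total under its proper name. It does not support calling it diet quality or tying it to dietetics alone.

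Third, component-level reporting may be set out in a statistical analysis plan that is not shown. It may be, but the protocol itself names the total score as the measure, so this is not merely a detail left open.

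A reader might also infer that weight loss from disease will show up as better diet. The protocol does not establish that. It gives no BMI or waist cut-offs, and loss in a lean man need not raise the score. Such loss is also not hidden: weight, body composition and the MST are recorded separately at screening and end of treatment, and nutritional risk is judged from body composition and the MST.

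A reader might wish to add that the 0.5% outlier flag for the food frequency questionnaire is unworkable in 72 men (0.005 × 72 = 0.36 per tail). The protocol does not say that the percentiles come from these men, it only flags the extremes, and section 6.2 separately screens all data for implausible and outlying values. That point is not made here.

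**Conclusion.** The point holds as a mismatch between endpoint and instrument. The total WCRF/AICR score can rise with no dietary change, and the protocol reads it as diet quality resulting from dietetics. It cannot be said that the score will rise for this reason: that depends on weights, cut-offs and baseline activity, none of which the protocol gives. The exercise route is the firmer one, because the programme itself supplies the activity.

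The 25% share outside diet rests on equal weights and on two of the eight recommendations being non-dietary. The 0.125 to 1.0 point range rests in addition on the illustrative f and p.

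The consequence is limited. This is a secondary endpoint, described rather than tested, in a feasibility study that was not sized for effects (sections 6.1 and 6.2), and no decision rule uses it. It should still be corrected, since the correction is cheap and the present label would mislead.

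**What to change.** In sections 3.4 and 4.4.4.1:

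1. Define the diet-quality endpoint as the sum of the food, drink and alcohol components of the WCRF/AICR score, and list those components.
2. Report BMI/waist and physical activity as separate components.
3. Report the total score descriptively, labelled as WCRF/AICR lifestyle adherence.

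The cost is wording only, because all components are already collected at screening and end of treatment. The sub-score is less comparable with published totals, but the total remains available for that purpose.

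The change does not solve attribution. With one arm and a combined programme, even a diet-only score cannot credit a change to dietetics alone, and the report should say so.

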#### 4.4.4.2 Quality of Life assessments

Quality of Life (QOL) will be assessed pre- and post- intervention (During screening/Week 0 and week 12 +/- 14 days), and 6 months post intervention. Provisionally, we plan on using the European Organisation for Research and Treatment of Cancer Quality of Life Questionnaire Core 30 (EORTC-QLQ-C30)); Quality-adjusted life-year (QALY) (EQ-5D-5L) and a measure of self-care agency/power to self-care (ASAS-R). These will be refined during the Scoping review to limit the number of questionnaires and ascertain the most pragmatic, reproducible and accurate assessment of QOL in this population. We seek to determine the effectiveness of the intervention on Quality of Life (core quality of life of cancer patients and disease). The Quality of Life assessments will provisionally (pending Scoping Review) include the following instruments:

**A) *The European Organisation for Research and Treatment of Cancer EORTC QLQ-C30*** comprises 30 items that can be summarized in 15 scales: Physical Functioning (PF), Role Functioning (RF), Social Functioning (SF), Emotional Functioning (EF), Cognitive Functioning (CF), Global QOL (QL), Fatigue (FA), Pain (PA), Nausea/Vomiting (NV), Appetite Loss (AP), Dyspnea (DY), Sleep Disturbances (SL), Diarrhoea (DI), Constipation (CO), and Financial Impact of Disease (FI). The disease specific HRQOL will be collected using EORTC modules for prostate, urothelial, kidney, penile and testicular cancer as required. These modules have undergone all of the EORTC phases of development (1–4), robust international psychometric testing and rigorous translations according to the EORTC standards.

**B) *QALY*** is a generic measure of disease burden, including both the quality and the quantity of life lived. It is used in economic evaluation to assess the value of healthcare interventions. For the economic evaluation, HRQoL is assessed using the EQ-5D-5L [15]. The EQ-5D-5L will be administered at T0, T12. The EQ-5D-5L consists of five questions evaluating the following health dimensions: mobility, self-care, usual activities, pain/discomfort, and anxiety/depression. The patients' EQ-5D-5L health states will be transformed into utility scores.

**C) *Appraisal Self-Care Agency***: The ASAS-R is used to measure self-care agency. The 15-item tool has three subscales Having power for self-care; Developing power for self-care and Lacking power for self-care [16].

**D) *Cancer related fatigue score***: The EORTC QLQ-FA12 standardised cancer related fatigue score will be used to measure cancer related fatigue at baseline, end of treatment and the 6 month follow up assessment to determine the impact of this type of intervention programme on cancer related fatigue.

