### **Data related to patient comorbidities, medication, and clinician record of actions/follow-up at survivorship and symptom management encounters:**

Data relating to resource utilisation will be collected on an ongoing basis for the study group. Data relating to survivorship services that were provided by CUH or UCC and used during the study period will be recorded. Data on service utilisation (outside of CUH) will be collected throughout the study period by the information provided from the patient through the study patient's reports at each session and the 6-month follow up; this will include the services used, frequency of use, duration of each service and the personnel responsible for providing the service. This information will be collected by the Research Nurse.

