| 24-hour Dietary Recall                                               | X                       |           |           |           |           |           |           |           |           |           |            |            |            | X   |                         |
| Food Frequency Questionnaire                                         | X                       |           |           |           |           |           |           |           |           |           |            |            |            |     | X                       |
| Programme Induction                                                  |                         | X         |           |           |           |           |           |           |           |           |            |            |            |     |                         |
| Nursing Assessment                                                   |                         | X         |           | A         |           | A         |           | A         |           | A         |            | A          | X          | X   | X                       |
| EORTC- QLQ-C30 Questionnaire                                         | X                       |           |           |           |           |           |           |           |           |           |            |            |            | X   | X                       |
| ASAS-R Questionnaire                                                 | X                       |           |           |           |           |           |           |           |           |           |            |            |            | X   | X                       |
| EORTC Cancer Related Fatigue Score                                   | X                       |           |           |           |           |           |           |           |           |           |            |            |            | X   | X                       |

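### The protocol gives three incompatible timings for EQ-5D-5L, the only source of the QALY endpoint, so utilities cover 0, 12 or 38 of the roughly 38 weeks of service-use data depending on which text is followed.

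*Protocol*

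**What the plan says.** Section 3.4 puts "Quality-adjusted life-year (QALY) (EQ-5D-5L") under endpoint 1 (quality of life) and again under endpoint 5 (resource utilisation). Section 2.3 makes the programme's economic impact a secondary objective. Item B of section 4.4.4.2 says that EQ-5D-5L supplies the health-related quality of life measure for the economic evaluation. No other instrument in the protocol yields utilities.

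Three places bear on its timing:

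- **Section 5.0, Schedule of Activities.** The table is said to fix when assessments are done. It has a row for "EORTC- QLQ-C30 Questionnaire", one for ASAS-R and one for the EORTC fatigue score, each marked at Screening, EoT and 6 months. No row or footnote names EQ-5D-5L.
- **Section 4.4.4.2, item B.** "The EQ-5D-5L will be administered at T0, T12".
- **Section 4.4.4.2, opening.** Quality of life is assessed before and after the intervention ("During screening/Week 0 and week 12 +/- 14 days), and 6 months post intervention"), and EQ-5D-5L is among the instruments then named.

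Service use outside the hospital is recorded from the "study patient's reports at each session and the 6-month follow up". Section 4.4.9 places that follow-up 6 months after the end of the 12-week programme.

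**The concern.** A team cannot follow all three texts at once. The Schedule is what staff work from, and section 4.4.6 refers to it for the timing of emailed survey links, so an electronic build that follows the table would leave out the only utility instrument. A team that follows item B would hold utilities to week 12 and service-use data for about six months longer, so QALYs and costs would cover different periods unless one were cut to fit the other. No later analysis plan can restore a questionnaire that was not given at its timepoint, which is why this belongs in the protocol.

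**Working it through.** The plan states no figure on this point, so there is none to reproduce. The check is a comparison of texts and one ratio.

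**Inputs**

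- Programme length: 12 weeks (section 4.3).
- Follow-up: 6 months after programme completion (section 4.4.9), taken as 26 weeks.
- Service use: collected at sessions and at the 6-month follow-up (section 4.4.4).
- T0 and T12: read as baseline and week 12. Baseline is taken as programme start, although Screening may fall up to 6 weeks before it.

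**Service-use window**

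12 + 26 = 38 weeks.

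**Coverage = weeks between first and last EQ-5D-5L ÷ 38**

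| Text followed | EQ-5D-5L at | Weeks covered | Share |
|---|---|---|---|
| Schedule alone | none | 0 | 0% |
| 4.4.4.2, item B | weeks 0, 12 | 12 | 12/38 = 31.6% |
| 4.4.4.2, opening | weeks 0, 12, 38 | 38 | 38/38 = 100% |

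Under item B, 26 weeks (26/38 = 68.4%) of service use has no utility measurement beside it. The most QALY one participant can accrue is about 12/52 = 0.23 over 12 weeks and 38/52 = 0.73 over 38 weeks, so the two horizons are not interchangeable.

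**Sensitivity of the item B share**

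- 6 months counted as 24 weeks: 12/36 = 33.3%.
- EoT assessment at week 14, the end of its allowed window: 14/38 = 36.8%. If the follow-up moves by the same two weeks: 14/40 = 35.0%.

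Item B thus covers about a third of the window under each of these choices.

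**Which text governs?** Item B is the more specific, and the fatigue item in the same section expressly names the 6-month assessment where item B does not. Against that, sections 3.2 and 4.3.2 give three general timepoints including 6 months, in line with the opening of 4.4.4.2. The protocol has no rule that ranks these texts.

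**Two lesser timing conflicts of the same kind**

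- 24-hour recalls: section 3.4 and the Schedule place them at baseline and end of programme. Section 4.4.4.1 reads "This includes two 24 Hour Dietary Recalls and a Food Frequency Questionnaire at baseline and month 6 (questionnaire follow up").
- QLQ-C30: section 3.4 says "EORTC QLQ C30 will be administered at baseline and at the end of the 12-week programme". The Schedule and the opening of 4.4.4.2 add 6 months.

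**The case against.** The strongest reply is that the instrument set is provisional pending the scoping review, that this is a feasibility study not sized for outcome effects, and that section 6.2 describes quality of life change only from baseline to end of programme, which T0 and T12 serve. The protocol also states no cost-per-QALY ratio, comparator or time horizon. Some of this stands: it keeps the matter at the level of secondary endpoints, and a deliberate 12-week horizon would be a legitimate choice. It does not remove the contradiction. QLQ-C30 and ASAS-R are equally provisional, yet both have Schedule rows, and a 12-week horizon is nowhere stated.

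Four stronger readings are tempting, and the documents do not support them.

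- **The QALY endpoint must end with either no data or 12 weeks of data.** The opening of 4.4.4.2 permits full coverage, and a missing row does not cancel the text that orders the questionnaire.
- **A fixed share of the QALY gain is lost.** Any such share depends on how the gain evolves after week 12. The protocol gives no such curve, and this single-arm study has no control group from which to identify a gain. Only the ratio of weeks comes from the document.
- **The dietary change in section 6.2 cannot be computed.** Section 4.4.4.1 itself opens with assessment at baseline and week 12 per the Schedule, which has the recall at EoT. The WCRF/AICR questionnaire and MST are also taken at Screening and EoT. The month-6 wording may be meant for the food frequency questionnaire alone.
- **The disease modules are missing in the same way.** The text says "The disease specific HRQOL will be collected using EORTC modules for prostate, urothelial, kidney, penile and testicular cancer as required" within the QLQ-C30 item, so the lack of a separate row is much weaker evidence of an omission.

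The QLQ-C30 conflict is also mild, since section 3.4 does not say that its two timepoints are the only ones.

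**Conclusion.** The inconsistency is real and should be fixed. The protocol gives three timings for the only instrument behind a QALY named under two secondary endpoints, and they imply utility coverage of 0, 12 or 38 of about 38 weeks of service-use collection. The 12-week reading covers 31.6% of the window, or 31.6% to 36.8% over the alternatives checked. These figures rest on reading T12 as week 12, treating baseline as programme start and taking 6 months as about 26 weeks. The absence of EQ-5D-5L from the Schedule rests on no assumption. The primary feasibility and acceptability endpoint is unaffected.

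**What to change.** Add an EQ-5D-5L row to the Schedule of Activities at Screening, EoT and 6-month follow-up, and change item B of 4.4.4.2 to the same three timepoints, so that utilities and resource use share one horizon. If 12 weeks is what the sponsor intends, state that horizon, add the row at Screening and EoT, restrict the costs to the same period, and exempt EQ-5D-5L from the 6-month timepoint in the opening of 4.4.4.2.

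In the same amendment, align the 24-hour recall timing in 4.4.4.1 with section 3.4 and the Schedule (end of programme), and the QLQ-C30 timing in section 3.4 with the Schedule (three timepoints).

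The cost is an amendment to one table and a few sentences, a matching change to any electronic survey build, and under the first option one five-question form at a 6-month contact that, according to section 4.4, already includes questionnaires. The change should be made before further participants pass the affected timepoints, because utilities not collected then cannot be recovered.
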